### Randomisation

A double-blind randomised placebo-controlled trial design has been chosen. Randomisation for the parallel treatment phase will be carried out by the pharmaceutical department after checking the inclusion- and exclusion criteria. The patient will be assigned to the treatment order as defined by the code. The patients will be randomised 1:1 according to the method of block randomisation with a block size of 10. No stratification is used. The study medication will be delivered in similar flagons and labels with its own sequence number. The allocation sequence number will be kept by the pharmacist in a secure place during the course of the study.

### Intervention

In this trial the dose of vitamin D (cholecalciferol) being supplemented is 50,000 IU. The consumption frequency will be once a month (equivalent to ~1667 IU/day in the treatment group) for six consecutive months. We chose the oral route of administration. Cholecalciferol is supplied in a vial of 8 ml containing 50,000 IU per ml, meaning the patients will use 1 ml per month. The placebo will be identical in taste, texture and appearance as the active supplement. The vitamin D supplement and placebo are manufactured and packed by the pharmacy of the Meander Medical Centre, Amersfoort, the Netherlands. Both the active supplements and the placebo will be given to participants in a translucent flagon with only their sequence number on the label. Labeling of the flagons will be done by the same person doing the randomisation and allocation sequence. A pipette of 1 ml will be delivered by the vial to make sure all patients use the right dose of the study medication. During their first visit patients will be instructed how to take in the study medication correctly with the pipette. To ensure compliance during the study, reminders about the intervention appointments will be sent regularly via email of phone calls.

The safety of vitamin D supplementation has well been established. The recommended dose for adults is 600–800 IU/day, depending on age, with an upper limit of 4,000 IU/day [31]. Toxicity of vitamin D supplementation did not occur with a dose of 10,000 IU/day [32]. Side effects (hypercalcaemia, hypercalcuria, renal stones, gastro-intestinal symptoms or hypersensitivity symptoms) of vitamin D supplementation are rare. For the safety of all patients serum creatinine and calcium are measured at three months. Patients with known hypercalcaemia are excluded for this reason. A 24 hour telephone number is available in the case hypersensitivity symptoms occur.

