#### Phase II

The trial has a total of three visits at the patient’s own general practice (Figure 1). The initial visit includes informed consent, assessment of eligibility, questionnaires regarding demographics, sunlight exposure, physical activity, dietary intake (fish and dairy products), diabetes history and medication, co-morbidity and health related quality of life (SF-36). Anthropometric parameters and skin AGE accumulation will be measured. Blood collection will be collect at this stage. The study medication will be given for six months with a prior instruction. The second visit at three months is for safety assessment and observation of consumption. This includes: discussion of any adverse events, any change in medication, control of the ingestion of the study medication, blood collection (including serum calcium, renal function, serum 25 (OH) D and HbA_1c_). The final visit is at the end of six months, when questionnaires and anthropometric measurements are repeated and the last set of blood samples are collected (Table 1). The inclusion of all patients will be spread over one year to prevent large seasonal influences, as well as the results will be adjusted for seasonal influences.

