** *Blood analysis* **			
Serum 25 (OH) D	x	x	x
HbA_1c_	x	x	x
Fasting blood glucose	x	x	x
Fasting blood insulin	x	x	x
C-peptide	x	x	x
Serum creatinine	x	x	x
Lipid profile	x		x
Serum calcium	x		x
Serum phosphate	x		x
Serum albumin	x	x	x
Serum PTH	x		x
Serum TSH	x		x
AST	x		x
ALT	x		x
Alkaline phosphatase	x		x
γ-GT	x		x
Hb, Platelets, Leukocytes	x		x
C-reactive protein	x		x
Urine analysis	x	x	x

All participants will be informed of their anthropometry and blood pressure measurement at the start and during the course of the trial. The blood test results during the course of the trial will only be discussed when these are abnormal and lead to premature termination of the trial. The following criteria are drawn for premature termination of the trial: hypercalcaemia (calcium > 2.65 mmol/l), onset of any granuloma forming disease, serum 25 (OH) D < 15 nmol/l or > 250 nmol/l, impaired renal function (eGFR < 30 ml/min), hypersensitivity for cholecalciferol, onset of urolithiasis, change in hypoglycaemic agents or HbA_1c_ > 69 mmol/mol (8.5%). After completion of the trial, all participants will be informed of their blood results. In case of vitamin D deficiency (serum 25 (OH) D < 50 nmol/l) at the end of the trial, supplementation with cholecalciferol will be started. The patients will be informed by letter in which group they participated after every patient completed the trial.

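### The text places serum calcium at the three-month visit but Table 1 marks it only at months 0 and 6, and a termination criterion depends on calcium

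*Protocol article*

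**What the plan says.** Calcium timing appears in three places in the protocol article.

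- Intervention, in the paragraph on safety: "For the safety of all patients serum creatinine and calcium are measured at three months".
- Phase II, on the three-month visit. Its purpose is given as follows: "The second visit at three months is for safety assessment and observation of consumption". The tests named for it are "blood collection (including serum calcium, renal function, serum 25 (OH) D and HbA_1c".
- Table 1, blood analysis block, with columns for months 0, 3 and 6. The calcium row is "Serum calcium x x", with marks under 0 and 6 and an empty cell under 3. The creatinine row is "Serum creatinine x x x", with a mark at every visit.

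The paragraph below Table 1 lists the criteria for premature termination, beginning with "hypercalcaemia (calcium > 2.65 mmol/l), onset of any granuloma forming disease".

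On timing, the supplement is taken monthly "for six consecutive months". There are three visits in all, and "The final visit is at the end of six months".

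**The concern.** A safety measurement is stated in the text and absent from the schedule table of the same document, and a termination criterion needs its result. The three-month visit is the only one between baseline and the end of treatment, so whether calcium is measured there decides whether the hypercalcaemia criterion has any scheduled value to act on while patients are still taking study medication. Calcium is also a named secondary outcome, and the reader cannot tell whether two or three time points are to be collected. Recruitment is still under way according to the Trial status section, and a three-month value that is not obtained at the time cannot be recovered later.

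**Working it through.** No sample size, power or error rate is involved, so the check is a side-by-side reading.

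**Step 1. Is the empty cell real?** Other rows with two marks, such as phosphate, PTH, TSH and lipid profile, have the same layout as calcium: a mark, an empty cell, a mark. Rows around them, such as creatinine and albumin, carry three marks. The gap at month 3 is therefore part of the table and not a fault of text extraction.

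**Step 2. Compare the tests behind the termination criteria.** Four of the criteria rest on a laboratory value in the schedule. Phase II names the tests for all four at month 3.

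| Termination criterion | Month 3 in Phase II text | Month 3 in Table 1 |
|---|---|---|
| Calcium > 2.65 mmol/l | yes | **no** |
| 25(OH)D < 15 or > 250 nmol/l | yes | yes |
| eGFR < 30 ml/min | yes (renal function) | yes (creatinine) |
| HbA1c > 69 mmol/mol | yes | yes |

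Text and table agree on three of the four. Calcium is the exception.

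**Step 3. Count scheduled calcium tests after baseline and before the final visit.**

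- Under Intervention and Phase II: 1 (month 3).
- Under Table 1: 0.

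**Step 4. What that means for the criterion.** Under Table 1 the only post-baseline calcium is at month 6. Assume that the first dose is taken at or soon after the first visit, when the medication is handed out. Six monthly doses then fall at about months 0, 1, 2, 3, 4 and 5, so all six precede the month 6 sample. A scheduled result at that visit comes too late to end treatment early. Under the text, a result is available at month 3.

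**Step 5. Does another section settle it?** The Blood collection section says that blood is drawn at 0, 3 and 6 months and includes calcium in its list of analytes. The same list includes PTH, TSH and lipids, which Table 1 has at 0 and 6 only. The list cannot be read as every test at every visit, so it does not decide the matter. The Outcomes section names calcium without a time point.

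**The case against.** The best case on the other side is that this is one missing mark in a summary table. Two text sections agree with each other, and one of them gives the reason for the test. Table 1 is captioned as a list of outcome variables and measurement times; nothing says that practices or the laboratory work from it. The case record form mentioned under data handling is not shown and may well list calcium at month 3. All of this stands, and it limits what can be concluded.

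A reader might infer more than the article supports:

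- **That calcium is never checked on treatment, so the criterion does not operate.** This needs Table 1 to be the governing document, which is not stated, and it sets aside two sections that do schedule the test. Calcium could also be measured outside the schedule if symptoms prompted it.
- **That up to 300 patients go unmonitored.** This only restates the empty cell. It also counts the placebo group; with 1:1 allocation about 300/2 = 150 patients receive cholecalciferol. Even on Table 1 alone, month 3 keeps creatinine, 25(OH)D, urine analysis and adverse events, so other safety criteria can still act.
- **That the secondary outcomes are damaged.** No mid-trial analysis of calcium is promised, and several secondary outcomes are measured only at 0 and 6 months.

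What the objection does not remove is the contradiction. A missing mark is plausible, but the article does not confirm it, and a stated safety criterion depends on the answer.

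**Conclusion.** The contradiction between text and table is certain. Its consequence is conditional. Its size is one scheduled calcium test per patient between baseline and the final visit under the text, against none under Table 1. If Table 1 is followed, the hypercalcaemia criterion has no scheduled on-treatment value to act on; if the text is followed, it has one. This rests on there being only three visits, as stated, and on the dosing times assumed above. It does not rest on any view of which schedule is correct, and the article gives no ground for saying that monitoring has failed. The point does not touch the primary outcome, the sample size, the randomisation or the analysis. It still deserves correction because it concerns a safety measurement tied to a termination rule and recruitment continues.

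**What to change.** Reconcile the Intervention section, the Phase II section and the calcium row of Table 1 so that one calcium schedule is stated throughout. Then make the case record form and the laboratory request form match it. The investigators must say which schedule was intended; this review does not choose between them. The change is a correction to one table cell or to two sentences of text, plus a check of the two forms.

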### Handling and storage of data and documents

For each participant a Case Record Form (CRF) is provided by the sponsor of the trial. All personal data are stored on a coded drive which is only available to the study coordination team. These documents will be stored in the hospital for a minimum of ten years. The Subject Identification Codes must be kept for at least 15 years. All these requirements are in accordance with the ‘Wet Medisch Onderzoek met Mensen’.

### Statistical analysis

The primary efficacy analysis to explore the intervention effect on glycaemic control will be based on the intention-to-treat (ITT) method, in which all randomised patients for whom outcome data are available, will be recorded. In the ITT analysis the patients will be analysed according to their original group assignment, whether or not they accepted and/or adhered to the intervention. This analysis avoids the possibility of any bias associated with loss, misallocation or non-adherence of participants. If there will be a substantial difference between those allocated to receive an intervention and those who actually received it (and adequately adhere to it), we will perform an additional analysis adjusting for actual treatment received (‘per protocol’ analysis). The results of the ‘per protocol’ analysis will be compared with the ITT analysis and the numbers involved will be precisely described.

All raw data will be entered into SPSS software (version 20.0, SPSS Inc, Chicago, IL). Ten percent of all data will be double-entered to check for duplication and outliers before starting statistical analyses.

Baseline characteristics of the study patients will be summarised separately for each randomised group. Dichotomous and categorical data will be presented as number and percentages of patients within both groups. Continuous variables will be checked for normality and will be presented in terms of means and standard deviation if normally distributed, or when a variable has a skewed distribution as median, 25th and 75th percentiles. Nominal variables including subgroups will be analysed using the Chi-squared test, ordinal variables by the Mann-Witney test or Kruskall-Wallis test and continuous variables by the *t*-test or analysis of variance model (ANOVA).

The primary efficacy endpoint, HbA_1c,_ will be compared between placebo and treatment group using a repeated measures analysis of variance with adjustment for baseline characteristics. For secondary outcomes a paired *t*-test, Wilcoxon’s test or repeated measures analysis of variance will be performed. Delta values will be calculated to compare the differences in means over time between the treatment and placebo group.

Correlation coefficients will be measured using Pearson or Spearman, depending on the level of measurement. A logistic and/or linear regression model will be used for multivariate analysis to relate an outcome variable to causal variables. The multivariate analysis will be used to rule out the possible role of confounders for vitamin D deficiency as season of measurement, maternal age, ethnicity, diet, physical activity and BMI.

Subgroup analyses will be performed by stratifying vitamin D into three groups: deficient (15–49 nmol/l), insufficient (50–74 nmol/l), and sufficient (75–150 nmol/l). Furthermore, subgroup analyses for vitamin D deficient patients (serum 25 (OH) D 15–35 nmol/l), and poor glycaemic control (HbA_1c_ ≥ 53 mmol/mol) will be performed using the same method as described for the primary analysis. A p-value < 0.05 will be considered as statistical significant.

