**Methods/design:**

In a randomised double-blind placebo-controlled trial conducted in five general practices in the Netherlands three hundred patients with type 2 diabetes mellitus treated with lifestyle advises or metformin or sulphonylurea-derivatives are randomised to receive either placebo or 50,000 IU Vitamin D_3_ at monthly intervals. The primary outcome measure is the change in glycated haemoglobin level between baseline and six months. Secondary outcome measures include blood pressure, anthropometric parameters, lipid profile, insulin resistance, quality of life, advanced glycation end products and safety profiles. Quality of life will be measured by The Short Form (SF-36) Health Survey questionnaire. Advanced glycation end products are measured by an AGE-reader.

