### Outcomes

The primary outcome of the study is HbA_1c_. Secondary outcomes are insulin resistance and beta-cell function measured by the homeostasis model of assessments (HOMA) and quantitative insulin sensitivity check index (QUICKI). Further secondary outcomes include the alteration of serum 25 (OH) D over time, blood pressure, lipid profile, parathyroid hormone, calcium, thyroid function, AGE accumulation in the skin, safety profile of vitamin D supplementation, urine analysis for microalbuminuria, and quality of life assessed by The Short Form (SF-36) Health Survey questionnaire.

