### Sample size estimation

It was calculated that 126 patients with T2DM would be required in this trial to demonstrate a significant difference at 80% power and 5% significance. Power calculations were based on the literature and aimed at a difference of 0.5% in HbA_1c_ value in the treated group as compared to the placebo group with a standard deviation of 1.0% [30]. With an expected rate of 50% vitamin D deficient participants, 252 subjects would be required. According to an expected drop out rate of 20%, 300 subjects will be recruited.

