### Blood collection

Venous blood sampling will be drawn at 0, 3 and 6 months by registered staff nurses using a sterile vacutainer needle between 8.00 and 9.30 am. All participants will be asked to fast overnight for at least 8 hours before blood collection. Blood serum will be used for the analysis of HbA_1c_, C-peptide, fasting insulin, calcium, phosphate, albumin, PTH, liver enzymes, lipid profile, C-reactive protein, TSH, platelets count, leukocytes and hemoglobin and 25 (OH) D ((iSYS automated immunoanalyser (IDS GmbH, Frankfurt, Germany)). The total 25-OH vitamin D assay detects 25-OH VD3 and 25-OH VD2, both with a specificity of 100%. The quality of the test is controlled by applying Westgard QC-rules on 3 different QC-samples [33]. The accepted interassay coefficients of variation are <10% for all 3 QC-samples (low, medium and high level). TSH and intact-PTH will be determined on a Beckman Coulter UniCel DxI 600 Synchron Access immunoanalyser (Beckman Coulter Nederland B.V., Mijdrecht, the Netherlands). Calcium, phosphate, glucose, albumin, liver enzymes, C-reactive protein and lipid profiles will be determined on a Beckman Coulter UniCel DxC 860i Synchron Clinical system chemistry analyzer. C-peptide and insulin will be determined on Siemens Immulite XPi automated immunoanalyser (Siemens Medical Solutions Diagnostics B.V., Breda, the Netherlands). HbA_1c_ will be measured on a HA-8180 automated HPLC system Menarini (Florence, Italy). The total white blood cell count, platelets count and haemoglobin content will be performed with an automated Sysmex XE-2100 blood cell counter (Sysmex Coorperation, Kobe, Japan).

Fasting blood glucose will be measured in blood plasma. Homeostasis model assessment of insulin resistance (HOMA-IR), calculated by fasting glucose (mmol/l) x fasting insulin (IU/ml)/22,5 and QUICKI, calculated by 1/log (fasting insulin (IU/ml)) + log (fasting glucose (mg/dl)), will be used to evaluate insulin resistance. Pancreatic beta-cell function will be assessed through the HOMA-B, calculated by (20 x fasting insulin (IU/ml))/(fasting glucose (mmol/l) – 3,5). All assays will be performed according to the manufacturer’s instructions and carried out by the central chemical laboratory of the Medical Centre Alkmaar, the Netherlands. This laboratory is a certified CCK laboratory. Aliquots of serum and plasma will be stored at -70/80’C for future research questions.

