This trial has several strengths: the study sample size allows us to perform a subgroup analysis of vitamin D deficient patients. Taken into account that only in vitamin D deficient patients an effect of vitamin D supplementation on glycaemic control will be found, we chose to recruit double the number of participants as calculated with the power estimation, hypothesizing that 50% of the included patients will be vitamin D deficient (serum 25 (OH) D < 50 nmol/l). Secondary, the relatively high dose chosen for intervention and the duration of the trial are strengths of our study. The dose of vitamin D supplementation of 50,000 IU of vitamin D per month (daily equivalent ~1667 IU) is based on the recommendations of the Institute of Medicine and on the study done by van Groningen et al. [31,34]. In this latter study, performed in the Netherlands, it was demonstrated that a cumulative dose of 100,000 IU given in 2 months increases the serum 25 (OH) D meanly with 29 nmol/l. Assuming that the mean serum 25 (OH) D in our study population will be around 50 nmol/l at baseline, the serum 25 (OH) D should be raising to a sufficient status (≥75 nmol/l) in two months. To measure a difference in HbA_1c_ level we hypothesize that the maximal effect will be seen at least at six months, regarding the fact that the red blood cells circulate about 100 days in the blood and HbA_1c_ levels takes around six weeks to change. Furthermore, this is the first study examining the association between vitamin D status and skin autofluorescence value as well as the effect on skin AGEs after vitamin D supplementation. For this secondary outcome the duration of our trial will be a limitation, regarding the stability and long half-life of skin AGEs with could be the cause to find no effect of vitamin D supplementation on skin AGEs.

The results of this trial should provide more insight into the potential causal association between vitamin D status and glycaemic control in patients with T2DM.

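### The primary HbA1c analysis does not name the effect of the repeated measures ANOVA that decides the trial, so it is not tied to the stated six-month change

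*Protocol article*

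**What the plan says.** - Abstract, Methods/design: "The primary outcome measure is the change in glycated haemoglobin level between baseline and six months".
- Outcomes: "The primary outcome of the study is HbA_1c", with no time point and no mention of change.
- Blood collection: "Venous blood sampling will be drawn at 0, 3 and 6 months". Table 1 lists HbA1c at all three visits.
- Statistical analysis, primary endpoint: HbA1c "will be compared between placebo and treatment group using a repeated measures analysis of variance with adjustment for baseline characteristics". The visits that enter, the deciding effect and the baseline variables are not named.
- Statistical analysis, secondary outcomes: "For secondary outcomes a paired *t*-test, Wilcoxon’s test or repeated measures analysis of variance will be performed". The next sentence adds: "Delta values will be calculated to compare the differences in means over time between the treatment and placebo group". It names no visit and is not called the primary test.
- Sample size estimation: the calculation "aimed at a difference of 0.5% in HbA_1c_ value in the treated group as compared to the placebo group with a standard deviation of 1.0" percent, giving 126 patients. It does not say whether that standard deviation belongs to the value or to the change.
- Discussion, on the timing of the HbA1c response: "we hypothesize that the maximal effect will be seen at least at six months".
- The last paragraph of the analysis text applies the primary method to the subgroups with low vitamin D and with poor glycaemic control.

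**The concern.** A repeated measures ANOVA on three visits has two standard between-arm F tests. One is the group main effect, which averages the arm difference over the visits. If baseline is one of those visits, a true difference of zero is averaged in. The other is the group-by-time interaction on 2 degrees of freedom, which asks whether the arms diverge in any pattern. Neither is the difference in change from baseline to month 6.

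The article therefore names an endpoint and a method but not the link between them. Different analysts could follow the same sentence and report different primary p-values, some from a diluted effect. The choice could also be made after the data are seen. The subgroup analyses use the same method, so the ambiguity reaches the vitamin D deficient patients for whose sake the sample was doubled.

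For secondary outcomes, a paired t-test, or a Wilcoxon test used as its counterpart, compares visits within an arm and does not test the treatment. The text lists these tests beside a between-arm method and gives no rule for choosing.

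**Working it through.** **Inputs from the article.** Difference 0.5, SD 1.0, 80% power, 5% significance, 1:1 allocation, HbA1c at months 0, 3 and 6.

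**Assumptions not in the article.** Two-sided test; SD 1.0 at each visit; equal correlation r between visits, from 0.5 to 0.8; arm difference at month 3 (d3) of 0, 0.25 or 0.5; no true difference at baseline; complete data.

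**Step 1: the plan's own figure.** n per arm = 2 × [(1.96 + 0.84) × 1.0 / 0.5]² = 62.8, so 63 per arm and 126 in total. The stated 126 reproduces, with 80.1% power by the normal approximation. It is a plain two-sample comparison of means, not a repeated measures calculation.

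**Step 2: power by reading, at n = 63 per arm.** Noncentrality λ = (n/2) × effect² / variance, with n/2 = 31.5, referred to the noncentral F distribution.

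- (a) Main effect over months 0, 3, 6: effect (0 + d3 + 0.5)/3, variance (1 + 2r)/3.
- (b) Group-by-time, 2 df: λ = 31.5 × (sum of squared deviations of 0, d3, 0.5 from their mean)/(1 − r).
- (c) Change from month 0 to month 6: effect 0.5, variance 2(1 − r). This equals the group-by-time test of a two-visit ANOVA.
- (d) Average of months 3 and 6 adjusted for baseline HbA1c: effect (d3 + 0.5)/2, variance (1 − r)(1 + 2r)/2.
- (e) Month 6 adjusted for baseline HbA1c (ANCOVA): effect 0.5, variance 1 − r².

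Worked case, r = 0.5 and d3 = 0.25:

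- (a) λ = 31.5 × 0.25²/0.667 = 2.95, power 40%.
- (b) λ = 31.5 × 0.125/0.5 = 7.88, power 71%.
- (c) λ = 31.5 × 0.25/1.0 = 7.88, power 79.5%.
- (d) λ = 31.5 × 0.375²/0.5 = 8.86, power 84%.
- (e) λ = 31.5 × 0.25/0.75 = 10.5, power 89.5%.

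Power over the whole range (first figure r = 0.5, second r = 0.8):

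| Reading | d3 = 0 | d3 = 0.25 | d3 = 0.5 |
|---|---|---|---|
| (a) Main effect, three visits | 21% to 17% | 40% to 32% | 62% to 51% |
| (b) Group-by-time, 2 df | 83% to 99.7% | 71% to 98% | 83% to 99.7% |
| (c) Change 0 to 6 | 79.5% to 99.3% | same | same |
| (d) Baseline-adjusted average of 3 and 6 | 50% to 78% | 84% to 98% | 97.6% to over 99.9% |
| (e) Baseline-adjusted month 6 | 89.5% to 99.6% | same | same |

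**Step 3: what reading (a) estimates.** (0 + 0 + 0.5)/3 = 0.17, (0 + 0.25 + 0.5)/3 = 0.25 and (0 + 0.5 + 0.5)/3 = 0.33, against a true month-6 difference of 0.5.

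**Step 4: sensitivity.**

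- At 60 per arm, the change test (c) has 78% power (r = 0.5) and 94% (r = 0.7), against 88% and 97% for (e): a gap of about 3 to 10 points.
- With a first-order autoregressive correlation of 0.7 or 0.8 and d3 of 0 or 0.5, the interaction is slightly ahead of (e): 91% against 89%, and 98% against 95%. With d3 = 0.25 it is behind: 69% against 89%, and 84% against 95%.

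**The case against.** A reader might infer that the plan commits to a test that cannot address the six-month change and always costs power. The article does not support that.

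- **The contrast is unnamed, not wrong.** A repeated measures ANOVA restricted to months 0 and 6 has a 1-df group-by-time test that equals the between-arm test of change. A three-visit model can also yield a month-6 contrast. Averaging in baseline would be an odd choice for an endpoint defined as a change. This stands.
- **The delta-values sentence is a between-arm comparison of change.** It follows the secondary tests directly, so the within-arm tests are not shown to be the only tests of effect. This stands, although the sentence fixes no visit, no baseline adjustment and no priority over the other listed tests.
- **Baseline HbA1c may be among the baseline variables adjusted for.** It may. A list of covariates could also sit in a fuller document, and its absence from an article is not the point here. The point is that the endpoint and the test, both stated in the article, are not joined.
- **Loss of patients with a missed visit is an inference.** Classical repeated measures ANOVA needs complete visits, but the article does not say that incomplete cases are dropped. Its intention-to-treat set is everyone randomised who has outcome data. A month-6 ANCOVA would also lose patients seen only at month 3. No finding is made on this.
- **The power loss is conditional.** It is severe only for the main effect over three visits. Reading (d) beats the month-6 comparison by up to 8 points if the full effect is present at month 3. The Discussion's expectation of a maximal effect at six months or later makes a smaller month-3 effect plausible but does not quantify it.

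**Conclusion.** The point holds as a gap in specification. The abstract's endpoint is the change to month 6, Outcomes gives no time point, and the analysis sentence leaves open which effect is tested and what role baseline HbA1c plays. Neither omnibus F test of a three-visit model is the month-6 contrast.

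The gap is large enough to matter because admissible readings of one sentence range from a badly underpowered trial to a well-powered one. At 63 per arm the main effect over three visits falls about 27 to 83 points short of the baseline-adjusted month-6 comparison. The 2-df interaction falls up to about 19 points short and in some patterns not at all. A test of the 0-to-6 change falls about 3 to 10 points short at correlations of 0.7 to 0.5. All of this rests on the assumed correlation and month-3 effect; only the reproduced 126 rests on the article's figures and a two-sided test alone.

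**What to change.** - **Primary test.** Name one: the between-arm difference in HbA1c at month 6, adjusted for baseline HbA1c. Preferably take it as the month-6 contrast of a linear mixed model on all available month-3 and month-6 values, with treatment, visit, treatment-by-visit and baseline HbA1c as terms. A month-6 ANCOVA on baseline is the simpler alternative.
- **Outcomes section.** State month 6, so that it agrees with the abstract.
- **Secondary outcomes.** Make the between-arm comparison of change in the delta-values sentence, adjusted for the baseline value, the test of effect. Keep within-arm paired t-tests and Wilcoxon tests as descriptive.

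The cost is analysis wording. The visits and baseline measurements are already scheduled and the sample size is unchanged. The wording should be settled before unblinding.
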